**Resistance training**						
Repetitions	20	20	15	15	10	10
Sets	2	2	2	3	3	3
Intensity	low (< 60% of 1-RM; RPE < 11)	moderate (60–70% of 1-RM; RPE 11–13)	moderate to high (70–80% of 1-RM; RPE 14–16)	moderate to high (70–80% of 1-RM; RPE 14–16)	high; until muscle fatigue (>80% of 1-RM; RPE > 16)	high; until muscle fatigue (>80% of 1-RM; RPE > 16)
**Coordination / Balance training**						
Dynamic (number of exercises)	1	2	3	3	3^a^	3^a^
Static (number of exercises)	1	1	2	2	3^a^	3^a^
**Endurance training**						
Duration	3–5 min	3–8 min	3–8 min	5–10 min	6–12 min	7–15 min
Intensity	low (RPE 10–12)	low (RPE 10–12)	moderate (RPE 12–14)	moderate (RPE 12–14)	moderate to high (RPE 12–15)	moderate to high (RPE 12–15)

*RPE* Rate of perceived exertion, *1-RM* 1-Repetition maximum

^a^same balance exercises, but with increased difficulty

In detail, the resistance training starts with the 2-month accommodation phase. This is followed by a period of regular exercise training with continuous progression of loads until the end of four months. Afterwards, sets and repetitions are further intensified during the last two months (intensified exercise training), when intensity aims to reach subjective muscle fatigue.

Additional coordination and balance training are planned as challenging training according to existing literature [21] and are continuously increased by complexity, difficulty and number of exercises. Coordination and balance are exercised statically on the floor or on a balance pad (AIREX Balance-pad, Switzerland) and dynamically on a balance-platform (HUR Smart Balance, HUR, Finland). This is added by endurance training performed on upright-bicycle and recumbent bicycle ergometers (HUR-Lode ergometers, HUR, Finland). This training will also be performed in a progressive manner regarding intensity and duration.

All training adaptations are communicated by the trainers and depend on the individual´s performance and previous progression. The subjective evaluation and progression of the intensity (resistance training and endurance training) is carried out and monitored throughout the whole training via the BORG scale and rate of perceived exertion (RPE) [25] (Table 1). The training is discontinued in case of safety issues or on participant´s request.

Before each training session, the participants’ state of health is queried and the training schedule is discussed. Training in small groups is intended to additionally foster the motivation to participate in the training on a regular basis. Adherence of the study participants is continuously documented by the exercise instructors during the intervention period. No additional home-based training sessions (exercises performed in the subject´s apartment or room) nor any other non-exercise components are planned. However, in case of any unpredictable short-term training cancellations due to lockdowns during the Corona pandemic, participants will be provided with an alternative home-training programme (i.e. brochure with functional exercises), if necessary. Our study protocol is in line with the Consensus on Exercise Reporting Template (CERT) [27].

#### Usual care

Study participants in the control senior care facilities receive usual care and will not be involved in any aspects of the bestform-training. Instead, the participants are offered 1–2 information meetings by trained study personnel or information brochures on the topic of “Healthy Ageing” during the six months study period.

### Outcome measures

Outcome measures are done at three time-points: baseline, after three months and after six months (end of intervention). Follow-up data will be collected by questionnaires after 18 and 30 months (Table 2).

**Table 2 Tab2:**
[figure not shown]
Enrolment, interventions and assessments in the bestform-trial (SPIRIT-Overview)

*MNA®-SF* Mini Nutritional Assessment—Short Form, *MoCA* Montreal Cognitive Assessment, *SARC-F* Screening tool for sarcopenia (questionnaire), *Short FES-I* Short Falls- Efficacy-Scale—International, *WHO-5* WHO-5 Well-Being Index

### Primary outcome

Primary outcome is the change of physical function between baseline and after six months of intervention, measured as the Short Physical Performance Battery (SPPB), a summary performance score out of three tests (standing balance test, gait speed test, and Chair-Stand-Test). For each participant the difference between six months to baseline will be used for analysis.

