### Secondary outcomes

Furthermore, secondary outcomes are:Change in SPPB after 3 months as compared to baselineChange in balance ability, mobility and risk of falling after 3 and 6 months as compared to baseline, measured by the Timed-Up-and-Go-Test and by stability tests on a balance platformChange of the 6-Minute-Walk-Test after 3 and 6 months as compared to baselineChange in handgrip strength after 3 and 6 months as compared to baselineMortality and rate of hospitalization over 6 monthsNumber of falls and fall-related injuries over 6 months, assessed by questionnaireChange in fear of falling (short FES-I), quality of life (WHO-5), nutritional status (MNA®-SF), risk screening for sarcopenia (SARC-F), physical activity and activities of daily living (Barthel-Index) recorded by questionnaires after 3 and 6 months as compared to baselineChange in fat free mass after 3 and 6 months as compared to baseline, measured by bioelectrical impedance analysisChange in calf and upper arm circumference after 3 and 6 months as compared to baselineChange in diastolic and systolic left ventricular myocardial function after 6 months as compared to baselineChange in proBNP after 3 and 6 months as compared to baselineChange in cognition after 6 months as compared to baseline measured by the MoCA

Further secondary endpoints are recruitment rate, adherence, drop-out and lost-to-follow-up rate as well as follow-up evaluation of SAEs, MACE, falls and fall-related injuries, and care degree after 18 and 30 months (Table 2).

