### Adverse and serious adverse events

The process evaluation comprises the documentation of recruitment rate and drop-out as well as lost-to-follow-up rate, the documentation of adherence to the training, and the documentation of adverse events (AEs) due to training (complaints while and immediately after training) and serious adverse events (SAEs).

AEs are defined as: Clinical events that occur during the training session or may possibly be related to the training intervention including accidents that occur during the training session or may possibly be related to the training intervention.

SAEs are defined as death, life-threatening events, events that lead to permanent damages or invalidity, or events that are followed by over-night hospitalisation.

AEs due to training and SAEs that occur during the study period irrespective of group assignment are documented in safety forms and transferred to a safety data base. In case of an SAE the principal investigator is directly informed and the procedure on further participation of the study determined e.g. study end, adaptations of the training, temporary or complete cessation of the training.

Throughout the course of the bestform trial, SAEs can be differentiated according to cardiovascular events and analysed separately. MACE are cardiovascular death, non-fatal stroke, and non-fatal myocardial infarction (3-point MACE). MACE and all-cause mortality will be documented during the study and the follow-up phase.

A questionnaire for falls documentation is used at the examinations ex1-ex3, in which the falls and fall-related injuries of the participants are recorded (Additional file 1: Supplement). A falls diary is not applied. Additional documentation is carried out by staff of the senior care facilities or by the trainers in the intervention care facilities (Table 2).

All participants are followed until end of study. A list of SAEs is provided to the responsive Ethics Committee after the end of the study.

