### Statistical analysis

#### Sample size calculation – Number of participants

For the primary analysis, mean values in changes of the SPPB score are compared between study groups accounting for the cluster-randomised design. We hypothesise that the intervention group could present at least a difference in mean changes of one point compared to the control group, which is considered as clinically relevant [47, 48]. A within group standard deviation of 2.5 points is assumed [49, 50], translating to an effect size (Cohen’s d) of d = 0.4.

Under these assumptions, 100 participants are needed per group in an individually randomised trial (significance level of 5%, power of 80%, two-sided test). Assuming a mean cluster size of 25 participants and an intra-cluster-correlation (ICC) of 0.025 [51, 52], this sample size has to be multiplied by a Design Effect (DE) of 1.6 to account for the cluster-randomised setting [53], resulting in a sample size of 160 participants per group. As we assume that about 20% of the included individuals will not provide data at the six months assessment, the sample size is increased to 400 individuals in total. To achieve this  ≥ 20 senior care facilities is planned to be recruited.

For the primary analysis comparing the mean values of changes in the SPPB score between the study groups, a mixed effects linear regression model with fixed effect for study group and baseline SPPB score and random cluster effects (senior residences) will be fitted to the data in order to account for within cluster correlation introduced by the cluster-randomised design [54]. The estimated mean difference between the study groups will be represented by the estimated regression coefficient for study group. The null hypothesis of no group difference will be tested two-sided on a significance level of α = 0.05 and a 95% confidence interval for the difference between group mean values will be estimated and presented. Means and standard deviations for both groups will be shown.

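### The primary model uses one 6-month change score per participant, so the roughly 20% expected without 6-month data contribute nothing, and the 3-month SPPB that could reduce any resulting bias goes unused

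*Protocol article*

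**What the plan says.** All references are to the protocol article.

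- **Primary outcome** makes the analysis variable a single number per person: "For each participant the difference between six months to baseline will be used for analysis".
- **Statistical analysis** (under the sample size heading) fixes the model as "a mixed effects linear regression model with fixed effect for study group and baseline SPPB score and random cluster effects (senior residences"). There is no visit term and no participant term.
- **Outcome measures** schedules assessments at baseline, 3 months (ex2) and 6 months (ex3). **Secondary outcomes** lists change "in SPPB after 3 months as compared to" baseline. The 3-month SPPB is therefore collected, but it has no part in the primary model.
- **Sample size calculation** assumes that "about 20% of the included individuals will not provide data at the six months assessment" and raises the total to 400 for that reason. The 20% is not divided by arm, reason or time of loss.
- **Adverse and serious adverse events** says that after an SAE the principal investigator is informed and "the procedure on further participation of the study determined e.g. study end, adaptations of the training" and so on. The same section also says: "All participants are followed until end of study".

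**The concern.** A model with one 6-month change per person can use only people who have that change. By the plan's own assumption about one participant in five does not. Some of them will have attended the 3-month examination, and that SPPB says something about where they were heading. The fixed model sets it aside.

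Recruiting more people replaces lost information. It does not make those who remain representative of those who were randomised. What is at stake is whether the primary estimate describes all included residents or only those still assessable at 6 months, and whether the selection differs between arms.

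A difference between arms is plausible. Only one arm trains twice weekly with rising intensity, and the controls are offered one or two information meetings or brochures. The discussion also expects higher morbidity and mortality, and difficulty with the training, in this age group. Plausible is as far as the document goes.

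The two SAE statements bear on the same question, because they leave open whether a 6-month SPPB is still sought after an SAE.

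**Working it through.** **1. The plan's own figures reproduce.** Inputs from the sample size section: difference 1 point, SD 2.5, two-sided 5%, power 80%, cluster size 25, ICC 0.025, 20% without 6-month data.
- Individually randomised: 99 per group, given as 100.
- Design effect: 1 + (25 − 1) × 0.025 = 1.6, so 100 × 1.6 = 160 per group.
- Loss: 160 / (1 − 0.20) = 200 per group, 400 in total. Expected without a 6-month value: 0.20 × 400 = 80.
- With 160 completers per group the effective size is 160 / 1.6 = 100, and power is 80.7%.

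The inflation therefore does its job for precision.

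**2. What it does not cover.** Let p be the share missing in an arm, and g the mean change in completers minus the mean change in those missing. The completer mean differs from the full-arm mean by p × g, so, before baseline adjustment,

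bias = p(I) × g(I) − p(C) × g(C).

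The document gives no g and no split of p. Assumed values:

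| Missing, I / C | Gap g, I / C (points) | Bias (points) |
|---|---|---|
| 20% / 20% | 1 / 1 | 0.20 − 0.20 = 0 |
| 20% / 20% | 1 / 0 | +0.20 |
| 20% / 20% | 0 / 1 | −0.20 |
| 25% / 15% | 1 / 1 | 0.25 − 0.15 = +0.10 |
| 15% / 25% | 1 / 1 | 0.15 − 0.25 = −0.10 |

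**3. Large-sample simulation, loss driven by 3-month SPPB.** Assumed: SD 2.5 for the score; correlations baseline–3 months 0.70, baseline–6 months 0.65 and 3–6 months 0.80; true 6-month effect 1.0; 20% missing per arm; log-odds of dropout 0.5 to 1.0 per SD of worse 3-month SPPB. Clustering is left out, so this concerns bias only.

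| Where loss depends on 3-month SPPB | Model as planned | Also using 3-month SPPB |
|---|---|---|
| Intervention arm only | 1.08 to 1.15 | about 1.00 |
| Control arm only | 0.85 to 0.92 | about 1.00 |
| Both arms equally | about 1.00 | about 1.00 |

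**4. Limits of the remedy.**
- The last column assumes that everyone lost after baseline attended ex2. With slope 1.0 in the intervention arm only, if half of those lost also missed ex2 the 3-month-informed estimate is 1.07; if three quarters did, 1.11.
- A harsher set of assumptions puts SD 2.5 on the change itself, with a 3- to 6-month correlation of change of 0.6, a 3-month effect of 0.5 and slope 1. Loss driven by 3-month change in one arm then gives 1.26 (intervention arm) or 0.74 (control arm), and using ex2 returns both to 1.00.
- Under the same assumptions, but with loss driven by the unseen 6-month value, the planned model gives 1.44 or 0.57. Using ex2 gives 1.29 or 0.71, so the bias is only partly removed.

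**5. The SAE statements side by side.** One sentence allows study end after an SAE. Another says all participants are followed until the end of the study. If study end means that assessments stop, the second sentence is not true of everyone. If it means something narrower, the text does not say so.

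**The case against.** **The article does not say completers only.** Analysis sets, imputation and sensitivity analyses usually belong to the analysis plan, which is not shown. Multiple imputation using the 3-month SPPB could feed exactly the stated model. This stands: the absence of those items is no finding. What remains is the model the article does fix, which gives a person without a 6-month value no outcome and has no place for the 3-month one.

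**A reader might infer that the dropout is informative and that the result will favour training.** The document does not support that. It gives about 20% overall, without arm or reason; it attributes morbidity to the whole age group; an equal mechanism leaves essentially no bias; and reversing the arms understates the benefit.

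**The bias is small beside the sampling error.** At 100 effective participants per arm the standard error is 2.5 × √(2/100) = 0.35, so 0.08 to 0.15 is about 0.23 to 0.42 of one standard error. That is fair. Unlike sampling error, however, bias does not shrink with a larger sample. The main simulation also uses an SD of change of 2.5 × √(2 − 2 × 0.65) = 2.09, below the 2.5 planned for changes.

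**The planned model is a standard choice and the remedy is incomplete.** Both are true. The proposal is a cheap improvement on data already collected, not the correction of an invalid method.

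**Follow-up is already promised, and mortality and drop-out are secondary endpoints.** This helps, but the promise conflicts with the study-end option in the same section.

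**Conclusion.** The point holds in a limited form. The fixed primary model leaves out everyone without a 6-month SPPB, about 80 of 400 on the plan's own assumption, and ignores their 3-month values. Raising the total to 400 protects power but not validity.

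Bias is possible but not demonstrated. It is about 0.1 to 0.15 points in either direction against a 1-point target if loss follows 3-month function in one arm only, and about zero if the mechanism is the same in both. The harsher assumptions in the working give larger values. Every one of these sizes rests on assumed correlations, dropout slopes or gaps that the document does not give.

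Using the 3-month SPPB removes the bias only where loss depends on observed values and ex2 was attended. It does not settle how deaths are handled. The conflict between the two SAE statements is in the text itself and does not depend on any assumption.

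**What to change.** 1. Make the primary analysis a longitudinal linear mixed model on the 3- and 6-month SPPB changes. Fixed effects: baseline SPPB, visit, group and group-by-visit. Add a random facility effect and a within-participant covariance. Include everyone with ex2 or ex3, and take the 6-month group contrast as the primary estimate.
2. Keep the current single-change model as a sensitivity analysis.
3. Report deaths by arm beside the SPPB result, since neither model settles what a 6-month score means after death.
4. Reconcile the two statements in the adverse events section, so that it is clear whether outcome data are still sought after an SAE. Which clinical rule applies is for the trial team to decide.

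Cost: a change of wording, slightly more modelling and an assumption about the within-participant covariance. No new data are needed, and the planned 400 does not change.

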### Secondary outcomes

Furthermore, secondary outcomes are:Change in SPPB after 3 months as compared to baselineChange in balance ability, mobility and risk of falling after 3 and 6 months as compared to baseline, measured by the Timed-Up-and-Go-Test and by stability tests on a balance platformChange of the 6-Minute-Walk-Test after 3 and 6 months as compared to baselineChange in handgrip strength after 3 and 6 months as compared to baselineMortality and rate of hospitalization over 6 monthsNumber of falls and fall-related injuries over 6 months, assessed by questionnaireChange in fear of falling (short FES-I), quality of life (WHO-5), nutritional status (MNA®-SF), risk screening for sarcopenia (SARC-F), physical activity and activities of daily living (Barthel-Index) recorded by questionnaires after 3 and 6 months as compared to baselineChange in fat free mass after 3 and 6 months as compared to baseline, measured by bioelectrical impedance analysisChange in calf and upper arm circumference after 3 and 6 months as compared to baselineChange in diastolic and systolic left ventricular myocardial function after 6 months as compared to baselineChange in proBNP after 3 and 6 months as compared to baselineChange in cognition after 6 months as compared to baseline measured by the MoCA

Further secondary endpoints are recruitment rate, adherence, drop-out and lost-to-follow-up rate as well as follow-up evaluation of SAEs, MACE, falls and fall-related injuries, and care degree after 18 and 30 months (Table 2).

### Examinations and assessments

The following examinations are planned at baseline (ex1), after three months (ex2) and after six months (ex3) of the intervention on an individual basis. Echocardiography, the coordination test on a balance platform, and the Montreal Cognitive Assessment (MoCA) [28] will only be assessed at ex1 and ex3. Questionnaires are conducted by interview by trained study staff.

A follow-up questionnaire (Serious adverse events (SAEs), Major adverse cardiac events (MACE) [29], falls, fall-related injuries, care degree) is planned after 18 and 30 months.

#### Anthropometric parameters

The assessment of anthropometric parameters includes weight, height, calf and upper arm circumference as well as body composition, e.g. skeletal muscle mass, measured by bioelectrical impedance analysis (BIA) (Tanita MC-780 MA S; Tanita Europe B.V., Netherlands).

### Assessment for primary endpoint—Short physical performance battery

The Short Physical Performance Battery (SPPB) [30, 31] is based on the tests listed below. For each test 0 to 4 points will be given depending on the performance and of these a SPPB summary score is calculated (0 to 12 points). The higher the score the higher the physical performance.

#### Standing balance test

The standing balance test is a coordination and balance test consisting of three exercises. Duration for each test is 10 s: 1.) Side-by-side position, 2.) Semi-tandem position and 3.) Full-tandem position. Difficulty of the tests is increasing from 1 to 3. Time is documented in all positions until 10 s are completed or the test is prematurely ended. For the first and easiest test to perform (side-by-side position), participants position their feet side by side (parallel in full contact). If the participant is not able to hold the position for 10 s, the complete test is ended and no further tests are started resulting in a standing balance test score of 0 points. If the participant is able to complete the first test, the semi-tandem position is performed next. Also, if the participant is not able to perform the semi-tandem position for 10 s, no further balance tests are started. If the semi-tandem test is successfully completed, then the full-tandem position is conducted.

#### 4 m-walking-test

The 4 m-Walking-test assesses gait speed [32]. The test starts from a standing position and ends when one foot has completely passed the finish line. Participants should perform the test in their habitual gait speed. The faster result of two attempts is used for calculation of a point score (1 to 4 points). If participants are unable to perform the 4 m-Walking-Test, the score will be 0 points. The use of any walking aids (canes, walkers or crutches) is documented.

#### Chair-stand-test

For the Chair-Stand-Test (CST), participants completely rise from a chair for five times as fast as they can. Arms are folded in front of the upper part of the body throughout the whole performance. The test starts with first rising from chair and ends with the final standing position at the end of the fifth repetition. If the participant is not able to rise without assistance of his/her arms or the time needed exceeds 2 min, the CST score is 0 points [33].

### Assessments for secondary endpoints

#### Timed-up-and-go-test

The Timed-Up-and-Go-Test (TUG) is a functional test to uncover gait disorders (muscle function) [34, 35]. The participant sits on a chair. After a start commando, the participant tries to stand up, goes three meters, turns around and sits back down on the chair. The required time is documented in seconds. The use of an assistive device (e.g. cane or walker) is allowed and is documented.

